### Outcomes

The primary outcome is a composite outcome of VP-shunt implantation, all-cause mortality, or EVD-related infection within 6 months after ictus. EVD-related infection is defined as a positive CSF culture, the use of intrathecal or systemic antibiotics for EVD-related infection, or both  (Table 1).

**Table 1 Tab1:** Outcomes of the DRAIN clinical trial

Outcomes	Type of data

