**Methods:**

DRAIN (*Danish RAndomised Trial of External Ventricular Drainage Cessation IN Aneurysmal Subarachnoid Haemorrhage*) is an international multicentre randomised clinical trial comparing prompt closure versus gradual weaning of the EVD after aSAH. The primary outcome is a composite of VP-shunt implantation, all-cause mortality, or EVD-related infection. Secondary outcomes are serious adverse events excluding mortality and health-related quality of life (EQ-5D-5L). Exploratory outcomes are modified Rankin Scale, Fatigue Severity Scale, Glasgow Outcome Scale Extended, and length of stay in the neurointensive care unit and hospital. Outcome assessment will be performed 6 months after ictus. Based on the sample size calculation (event proportion 80% in the gradual weaning group, relative risk reduction 20%, alpha 5%, power 80%), 122 participants are required in each intervention group. Outcome assessment for the primary outcome, statistical analyses, and conclusion drawing will be blinded. Two independent statistical analyses and reports will be tracked using a version control system, and both will be published. Based on the final statistical report, the blinded steering group will formulate two abstracts.

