## Methods

The DRAIN trial is an international multi-centre, 1:1 randomised, parallel-group, superiority clinical trial investigating gradual weaning versus prompt closure of EVD in patients with hydrocephalus following aSAH. The trial was registered at ClinicalTrials.gov with identifier no. NCT03948256 before inclusion of the first patient. The detailed trial protocol has been published elsewhere [9]. In short, all adult patients admitted to one of the participating neurosurgical departments with a diagnosis of aSAH and a need for EVD placement will be screened for enrolment. Each trial participant is allocated a unique patient trial number. Following successful treatment of the ruptured aneurysm, in eligible participants, the EVD resistance will be set to 10 cm H_2_O to ensure a uniform drainage production prior to intervention. An increase of drainage resistance to 15 cm H_2_O may be done if a high drainage volume is the only factor that keeps the patient from being randomised. When the participant fulfils all the inclusion criteria and none of the exclusion criteria, they will be randomised, and the allocated intervention (gradual weaning versus prompt closure) will be initiated immediately hereafter. Participants must fulfil the inclusion criteria within 18 days after ictus in order to be included in the trial. This statistical analysis plan follows the guidelines for statistical analysis plans [10].

Inclusion criteria:

> 18 years of ageDiagnosis of aneurysmal subarachnoid haemorrhage (aSAH)External ventricular drain (EVD) for > 6 daysaDrain output of < 220 mL/day at a resistance of 10 or 15 cm H2OStable or improving Glasgow Coma Scale (GCS) > 9 during the last 24 hSigned informed consent (from patient or next-of-kin)

Exclusion criteria:

Severe pre-existing (physical or mental) disability or severe co-morbidity that would lead to poor outcome even if the patient made a full recovery from the aSAHLife expectancy shorter than 48 hours after admission

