**Secondary outcomes**	
SAE excl. mortality within 6 months after aSAH	Count
Health-related quality of life (EQ-5D-5L) at 6 months with the primary assessment being self- assessment of own health (EQ VAS; 0 to 100 point scale)	Continuous
Mean Fatigue Severity Scale (FSS) score at 6 months (1–7 levels)	Continuous

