### Sample size and power justification

#### Sample size estimation

Data from the only previous randomised clinical trial suggest a VP-shunt implantation proportion of 63% in patients with acute need of CSF diversion following aSAH [5]. The mortality following aSAH is commonly quoted to be 27% to 50%, while 5.8% of patients develop an EVD-related infection [2, 7]. Assuming an incidence of either of the three components of the composite primary outcome (VP-shunt implantation, all-cause mortality, or EVD-related infection) within 6 months of 80%, an *α* = 0.05 (two-sided), and a *β* = 0.20, 2 × 122 participants are required to detect a 20% relative risk reduction or increase calculated using R (R Core Team, Vienna, Austria)*.* For composite outcomes, one missing component will result in missingness in the composite outcome. Number and percent missing due to a missing component will be stated in the report or in a diagram to avoid biased result, e.g. from death alone.

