#### Sensitivity analyses

The primary and secondary outcomes will also be analysed for the per-protocol population as sensitivity analyses. Furthermore, the primary outcome will be investigated based on 6 months after randomisation instead of ictus. Finally, the ordinal outcomes will also be analysed as dichotomous outcomes based on the dichotomisation presented above.

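### The primary and SAE windows start at ictus, so EVD infections and SAEs before randomisation count as outcomes; this attenuates the comparison modestly and adds noise, without favouring either arm

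*SAP article*

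**What the plan says.** The Outcomes section sets the primary endpoint: "The primary outcome is a composite outcome of VP-shunt implantation, all-cause mortality, or EVD-related infection within 6 months after ictus". Its infection component has no limit on onset: "EVD-related infection is defined as a positive CSF culture, the use of intrathecal or systemic antibiotics for EVD-related infection, or both". Table 1 lists the first secondary outcome as "SAE excl. mortality within 6 months after aSAH".

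The Methods section places randomisation well after ictus. One inclusion criterion is an EVD in place for more than 6 days, and "Participants must fulfil the inclusion criteria within 18 days after ictus in order to be included in the trial". Once a participant is randomised, "the allocated intervention (gradual weaning versus prompt closure) will be initiated immediately hereafter". The two listed exclusion criteria concern severe prior disability or co-morbidity and a very short life expectancy. Neither removes a patient who has already had an EVD infection.

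Under Sensitivity analyses, "the primary outcome will be investigated based on 6 months after randomisation instead of ictus". The sentence does not say whether earlier events are dropped or only the end of the window moves. It does not cover SAEs.

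**The concern.** The outcome clock starts roughly 6 to 18 days before the two strategies can differ. Read literally, a participant with a positive CSF culture on day 5 who is randomised on day 10 already has a primary event, whatever happens under the allocated strategy.

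This matters most for infection. The Abstract and Introduction present infection from longer drainage as the main risk of gradual weaning, and only infections after randomisation can test that. For SAEs, complications of the acute illness before randomisation enter a count that is meant to compare the two strategies. Events that allocation cannot influence pull relative effects towards no difference, and chance imbalance in them adds noise.

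**Working it through.** **Which components are exposed.** A participant who is randomised cannot have died earlier. With the EVD still in place, a prior VP shunt is not expected. That leaves infection within the composite, and SAEs.

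**Inputs from the SAP article.** The Abstract gives "event proportion 80% in the gradual weaning group, relative risk reduction 20%, alpha 5%, power 80"%, so the planned risks are 0.80 and 0.80 × 0.80 = 0.64. There are 122 per group and alpha is two-sided 0.05 (Sample size estimation). The infection rate is "5.8% of patients develop an EVD-related infection" (same section). SAEs are planned with mean 3, SD 1.5 and difference 1 (Power estimations). The share of events before randomisation is not given, so it is an assumption throughout.

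**Step 1: reproduce the plan.** With pooled variance under the null and p̄ = 0.72:

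- n = [1.960 × √(2 × 0.72 × 0.28) + 0.842 × √(0.80 × 0.20 + 0.64 × 0.36)]² / 0.16² = (1.2445 + 0.5259)² / 0.0256 = 122.4. This agrees with the stated 122 up to rounding (123 if rounded up).
- Power at 122 per group = Φ[(0.16 × √122 − 1.2445) / 0.6248] = Φ(0.837) = 79.9%.

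**Step 2: composite.** Let a share q of each arm have had an infection before randomisation, independently of later risk. The counted risk is q + (1 − q) × p, so the risk difference shrinks by the factor (1 − q). For q = 0.029 (half of 5.8%):

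- gradual weaning: 0.029 + 0.971 × 0.80 = 0.806
- prompt closure: 0.029 + 0.971 × 0.64 = 0.650
- RR = 0.650 / 0.806 = 0.807

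| q (assumed) | Risks counted | RR | Power, 122 per group |
|---|---|---|---|
| 0 | 80.0% vs 64.0% | 0.800 | 79.9% |
| 2% | 80.4% vs 64.7% | 0.805 | 78.7% |
| 2.9% | 80.6% vs 65.0% | 0.807 | 78.2% |
| 5.8% | 81.2% vs 66.1% | 0.814 | 76.5% |
| 10% (stress value) | 82.0% vs 67.6% | 0.824 | 73.9% |

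This treats 80% as the risk after randomisation. If the 80% already includes the early infections and q = 5.8%, power is 74.1% with them counted and 77.6% without. The loss from the window is then 3.5 points, against 79.9 − 76.5 = 3.4 points in the table.

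**Step 3: infection component (exploratory).** Take 5.8% in total, half of it (2.9%) before randomisation, and a true halving afterwards. The counted risk in the better arm is 2.9% + 0.5 × 2.9% = 4.35%, and 4.35 / 5.8 = 0.75. The true RR of 0.50 appears as 0.75. With a quarter or three quarters early, it appears as 0.625 or 0.875.

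**Step 4: SAEs.** Keep the planned difference of 1 and SD of 1.5 for events after randomisation, and add early events as Poisson noise with mean m. The difference stays at 1 and the SD becomes √(1.5² + m). Power ≈ Φ[1 / (SD × √(2/122)) − 1.96]:

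- m = 0: SD 1.50, power 99.9% (the plan states 100%)
- m = 1: SD 1.80, power 99.1%
- m = 2: SD 2.06, power 96.6%
- m = 3: SD 2.29, power 92.6%

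The ratio of means moves from 2/3 = 0.67 to (2 + m)/(3 + m), that is 0.75 at m = 1 and 0.83 at m = 3.

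**The case against.** The best reply is that the harm is small and partly foreseen. Only infection, quoted at 5.8% in total, can contaminate the composite. The plan already has a randomisation-based sensitivity analysis of the primary outcome. The SAE and component results are declared hypothesis generating under General analysis principles. The stated window may be meant to fix only its end, with the start of event recording set in the separately published protocol, which is not shown. With 243 participants randomised, changing an outcome definition is not a trivial edit.

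Much of this stands and limits the point to a modest one. It does not remove it. The conclusion rests on the primary analysis, the sensitivity analysis does not say what happens to earlier events, and SAEs have no counterpart analysis.

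A reader might infer three stronger things that the documents do not support:

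- **Bias towards one arm.** Events before randomisation are balanced in expectation, so no direction follows.
- **A collapse in SAE power, to about 40%.** That figure needs the planned difference of 1 to be recast as a one-third reduction acting only on later SAEs, with two thirds of SAEs assumed early and the SD held at 1.5. Most of the fall comes from the smaller assumed effect, which a changed window would not restore.
- **Follow-up about 18 days short for the randomisation-based analysis.** Trial status expects inclusion to end in June 2024 and follow-up in December 2024. That is compatible with 6 months after randomisation, and shunt, death and infection need not be tied to a visit date.

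**Conclusion.** The concern holds as a defect of definition with a modest effect. As written, infections and SAEs that precede randomisation count as outcomes of the allocated strategy, and no rule in the article excludes them. For the composite, the RR moves from 0.80 to about 0.81, and power falls from 79.9% to 78.2% (half of infections early) or 76.5% (all early). The exploratory infection comparison is the most distorted, and SAE power stays above 92% in the range examined.

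All of these sizes rest on assumed early shares, on independence between early infection and later risk, and on the Poisson form of the early SAEs. The SAE figures use a comparison of means, whereas the plan analyses counts with the van Elteren test, so they are approximate.

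**What to change.** Before unblinding:

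1. Define the infection component and the SAE count as events with onset after randomisation and up to 6 months after ictus. The end date can stay as it is.
2. State that an infection already present at randomisation is not an outcome event, and apply the same rule to SAEs.
3. Report the counts from ictus as a sensitivity analysis for both outcomes.
4. State under Sensitivity analyses that the analysis based on 6 months after randomisation drops events before randomisation.

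The cost is a documented change to an outcome definition late in the trial, which should be dated and explained as made while blinded. The event count falls slightly. Onset dates for infections and SAEs are needed; the article does not say that they are recorded, so this should be checked first. The programming itself is a date filter.

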**Primary outcomes**	
The primary outcome is a composite outcome of VP-shunt implantation, all-cause mortality, or EVD-related infection 6 months after aSAH	Count

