VP-shunt implantation—*n* (%)	40 (33)	32 (26.2)	*mean diff (95%CI)* 34.4 (31.1 to 43.4)	0.03
Mortality—*n* (%)	4 (3.3)	2 (1.6)	*mean diff (95%CI)* 3.4 (-1 to 6)	0.06
Drain-related infection—*n* (%)	9 (7.4)	12 (9.8)	*mean diff (95%CI)* 10.4 (4.3 to 14)	0.05

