### Count data outcomes

Count data exploratory clinical outcomes will be presented as medians and interquartile ranges for each group, with an annotation in the tables of the percentage of missing data per group. Count data will be analysed using the van Elteren test from Stata or an equivalent in R [24, 25]. The results will be presented with median differences and Hodges-Lehmann confidence intervals to demonstrate the uncertainty of the results [26].

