### Dichotomous outcomes

Dichotomous outcomes will be presented as proportions for each group with an annotation in the tables of the percentage of missing data per group. Dichotomous outcomes will be analysed using mixed-effects logistic regression with stratification variables as fixed effect and site as random effects. We will estimate the marginal effects to obtain RRs and confidence intervals of the RRs (based on ‘nlcom’ from Stata (StataCorp LLC, Texas, USA)) or G-computation in R. We have chosen to—as a primary analysis—investigate our count outcomes without dichotomisation. Inappropriate dichotomisation—even though widely used—results in lower power and possibly also faulty results [28, 30, 31].

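### Table 1 types the yes/no primary composite as a count, so the SAP supports two primary analyses, and only one of them estimates the relative risk the trial was powered on

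*SAP article*

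**What the plan says.** The Outcomes section defines a yes/no event per participant: "The primary outcome is a composite outcome of VP-shunt implantation, all-cause mortality, or EVD-related infection within 6 months after ictus". Table 1 repeats it, as "The primary outcome is a composite outcome of VP-shunt implantation, all-cause mortality, or EVD-related infection 6 months after aSAH", and gives its type of data as *Count*. No row of Table 1 is typed dichotomous.

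Methods are assigned by data type:

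- **Count data outcomes:** "Count data will be analysed using the van Elteren test from Stata or an equivalent in R". For the effect measure: "The results will be presented with median differences and Hodges-Lehmann confidence intervals to demonstrate the uncertainty of the results".
- **Dichotomous outcomes:** "Dichotomous outcomes will be analysed using mixed-effects logistic regression with stratification variables as fixed effect and site as random effects", with RRs and their intervals obtained from marginal effects or G-computation. The same section says that the primary analysis will "investigate our count outcomes without dichotomisation".

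Neither section names the primary composite.

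The Abstract and the Sample size estimation section power the trial on an event proportion of 80%, a 20% relative risk reduction, two-sided alpha 0.05 and power 80%, giving 122 per arm. Table 3, which the Results section presents as the model for the final manuscript, shows the composite as n (%) with an RR. It labels VP-shunt, mortality, drain-related infection and clinical fatigue (FSS ≥ 4), all rows of counts with percentages, as *mean diff*; the VP-shunt row prints its estimate and interval as "34.4 (31.1 to 43.4". The SAE row is headed median (IQR) and shows 340 and 320.

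**The concern.** Because the method follows from the data type, the Table 1 entry is the only explicit link from the primary outcome to an analysis, and it points to a rank test with a median difference. The design and the results template point to an RR. Two statisticians are to work independently from this text, and each could defend a different primary analysis.

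The rule in Statistical reports for disagreement, to take the more conservative result, is written for similar or identical analyses. It does not choose between two effect measures. At stake are the effect estimate for the primary outcome and the prespecification that the article gives as its purpose.

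The reporting template adds to the doubt, because four binary rows carry an effect measure that the dichotomous section does not prescribe.

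**Working it through.** **1. The plan's own figure.** Inputs from the Abstract and Sample size estimation: p1 = 0.80, p2 = 0.80 × (1 − 0.20) = 0.64, mean 0.72, two-sided alpha 0.05, power 0.80.

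n = [1.960 × √(2 × 0.72 × 0.28) + 0.842 × √(0.80 × 0.20 + 0.64 × 0.36)]² / 0.16² = 122.4 per arm.

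The arcsine version gives 121.3, which rounds up to 122; power at 122 per arm by the pooled formula is 79.9%. The stated 122 is thus reproduced by a comparison of two proportions. A 20% relative increase (80% v 96%) needs 64 per arm, so the reduction governs.

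**2. The count route on a 0/1 outcome.** The Hodges-Lehmann estimate is the median of all between-arm pairwise differences. At 80% and 64%:

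| Difference | Probability |
|---|---|
| +1 | 0.80 × 0.36 = 0.288 |
| 0 | 0.80 × 0.64 + 0.20 × 0.36 = 0.584 |
| −1 | 0.20 × 0.64 = 0.128 |

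More than half of the differences are 0, so the median is 0. It was 0 in all 20,000 simulated trials of 122 per arm. For it to become 1, P(+1) must exceed 0.5. With 80% in one arm that means 0.80 × (1 − p2) > 0.5, so p2 below 37.5%, a relative reduction of more than 53% against the planned 20%.

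**3. One trial at about the design rates: 98/122 v 78/122.** Of 122 × 122 = 14,884 pairs, 24 × 78 = 1,872 give −1, 98 × 78 + 24 × 44 = 8,700 give 0, and 98 × 44 = 4,312 give +1. The zeros fill ordered positions 1,873 to 10,572.

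The large-sample interval runs from position 14,884/2 − 1.96 × √(14,884 × 245/12) ≈ 6,362 to about 8,523. Both ends are 0.

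| | Count route | Dichotomous route (crude) |
|---|---|---|
| Group summary | medians 1 and 1 | 80.3% and 63.9% |
| Effect | 0 (0 to 0) | RR 78/98 = 0.796 |
| p-value | 0.0044 (rank test) | 0.0043 (chi-square) |
| Simulated power at 80% v 64% | 80.5% | 80.5% |

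Test and power are practically the same; the effect estimate is lost.

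**4. Table 3 labels.** Components and clinical fatigue are n (%) rows, for which the dichotomous section prescribes RRs, but they are labelled mean differences. For SAE, 340/122 = 2.8 and 320/122 = 2.6 per participant, close to the mean of 3 (SD 1.5) assumed under Power estimations. The two figures look like arm totals and cannot plausibly be per-participant medians.

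**The case against.** The case for leaving the plan alone is that its intention is clear enough. The sample size and the composite row of Table 3 both indicate an RR, the dichotomous section gives the only route to one, and a single table cell points elsewhere. The remark about not dichotomising count outcomes is aimed at multi-level outcomes; a composite that is already 0/1 cannot be dichotomised further. The median and interquartile presentation is worded for exploratory outcomes only ("Count data exploratory clinical outcomes will be presented as medians and interquartile ranges for each group"), and both blinded reports are compared and their discrepancies discussed. These points stand as to intention. They do not remove the contradiction: the van Elteren sentence covers all count data, and no sentence says which route the composite takes.

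Four stronger readings do not hold.

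- *The SAP abandons the RR.* It does not; it contradicts itself.
- *The count route costs power or distorts the test.* Step 3 shows that it does not.
- *The logistic model has no outcome to analyse.* The Sensitivity analyses section also analyses the ordinal outcomes as dichotomous, which leads to that model. The three components are not rows of Table 1, so they are not typed as counts there.
- *The Table 3 values reveal a faulty program.* Some printed differences equal or nearly equal the average of the two arms (340 and 320 give 330; 60 and 56 give 58). Others do not: VP-shunt 40 and 32 average 36 but 34.4 is printed, and clinical fatigue 88 and 82 average 85 but 3.4 is printed. The values are declared simulated and the report program is not shown, so only labels and layout can be criticised.

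Retyping the EQ-5D levels and discharge GCS as ordinal would be largely a preference. A rank test suits ordered scores, and the plan itself falls back on the count route for ordinal data.

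**Conclusion.** The point holds as a contradiction in the primary analysis. By its stated type the composite gets a median difference; by its sample size and results template it gets an RR; no method section decides. Under the count route the estimate at the design rates is 0 (0 to 0 in the worked example) where the crude RR is 0.80, while p-value and power (about 80%) hardly move. The harm is to the effect estimate and to prespecification, not to the significance test.

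This rests on the design rates of 80% and 64% and on unstratified calculations; the van Elteren test and the mixed-effects model, which use strata or site, may differ slightly from these figures. The Table 3 part is limited to the *mean diff* labels on four binary rows and the SAE row's arm figures under a median heading. Reason for failure, which is a nominal item, is also mistyped as a count.

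**What to change.** Before unblinding:

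1. In Table 1, type the primary composite as *Dichotomous*.
2. In the Dichotomous outcomes section, state that the composite and its three components are analysed by the mixed-effects logistic model already described there, reported as a marginal RR with 95% CI, and that for the composite this is the primary analysis.
3. Treat reason for failure of EVD cessation as separate yes/no items, one per reason.
4. In Table 3, relabel the three component rows and clinical fatigue as RR, and show the SAE row as per-participant medians with interquartile ranges.

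The cost is a few sentences, two table corrections and a check that the report program uses the same effect measures. The sample size is unchanged and no new data are needed.
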